### Eligibility criteria

2.2

Eligible participants will be adult patients scheduled to undergo robotic laparoscopic hysterectomy under general anesthesia. Based on the inclusion criteria, patients aged 19–65 years, with a body mass index (BMI) of 18.5–35 kg/m^2^, and of American Society of Anesthesiologists Physical Status (ASA-PS) I or II will be included. The upper age limit of 65 years was selected because aging affects cardiovascular physiology and anesthetic pharmacodynamics, thereby reducing population heterogeneity (Doi et al., 2020). Similarly, the BMI range of 18.5–35 kg/m^2^ was chosen because extremes of body weight are associated with altered pharmacokinetic and pharmacodynamic characteristics that may influence hemodynamic responses to anesthetic agents (Park et al., 2018; Kim, 2021). Patients will be excluded if they present with preoperative systolic blood pressure (SBP) ≥ 160 mmHg or <90 mmHg, heart rate (HR) < 60 beats per minute or ≥100 beats per minute, hypoxemia defined as oxygen saturation (SpO_2_) < 90%, or a history of ischemic heart disease, cardiac conduction abnormalities, or severe respiratory disease, including uncontrolled asthma or chronic obstructive pulmonary disease. Additional exclusion criteria will include the administration of inhalational anesthetics during anesthesia and intraoperative conversion from robotic laparoscopic hysterectomy to open surgery.

This single-center trial will be conducted at CHA Ilsan Medical Center, a university-affiliated secondary hospital equipped with advanced robotic surgical platforms and electronic anesthesia documentation systems. All anesthesia will be administered by board-certified anesthesiologists with ≥3 years of clinical experience in total intravenous anesthesia using propofol and remimazolam infusion techniques. Participating surgeons will be experienced in robotic laparoscopic hysterectomy, each having performed >50 procedures before study initiation.

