### Harms and criteria for discontinuation or modification

2.5

Remimazolam and propofol are routinely used intravenous anesthetics for robotic laparoscopic surgery at our institution. Therefore, participation in our trial is not anticipated to introduce additional risk. However, hypotension and bradycardia may occur following administration of sedatives or opioids, and hypertension or tachycardia may arise in response to surgical stimuli. Hypotension (SBP <90 mmHg or MAP <65 mmHg) will be managed by reducing the remifentanil infusion rate. Severe hypotension (SBP <80 mmHg or MAP <60 mmHg) will be treated with intravenous ephedrine 5–10 mg or phenylephrine 30–100 μg. Hypertension (SBP >140 mmHg or MAP >100 mmHg) will be managed by increasing the remifentanil infusion rate, whereas severe hypertension (SBP >160 mmHg or MAP >105 mmHg) will be treated with intravenous nicardipine 300–500 μg or labetalol 5–10 mg. Bradycardia (HR < 45 beats/min) will be treated with intravenous glycopyrrolate 0.2 mg or atropine 0.25 mg, and tachycardia (HR > 100 beats/min) will be managed using intravenous esmolol 10–20 mg.

Study interventions may be modified or discontinued in cases of severe hypotension (SBP <80 mmHg or MAP <60 mmHg) unresponsive to protocol-directed vasopressor therapy, severe bradycardia (HR < 40 beats/min) unresponsive to atropine or glycopyrrolate, severe hypoxemia (SpO_2_ < 90% for more than 1 min), a severe allergic reaction to study medications, or if the attending anesthesiologist determines that continuation of the assigned intervention is unsafe. In such situations, anesthesia may be transitioned to an alternative regimen at the clinician’s discretion, and the event will be documented in the case report form (CRF).

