### Data management

2.10

All study data will be documented in standardized, paper-based CRFs developed for this trial. The CRFs will be pilot-tested in five patients before study initiation to ensure feasibility, clarity, and internal consistency. To maintain data quality, study personnel will receive pre-study training on CRF completion and data handling procedures. Duplicate checks of key variables (hemodynamic parameters and anesthetic drug doses) will be conducted, and 10% of completed CRFs will be randomly audited against source documents by an independent investigator. Any discrepancies will be resolved by consensus.

Intraoperative hemodynamic variables recorded using the Vital Recorder system will be extracted into a structured Excel file, which will serve as the source data. Relevant parameters, including MAP, HR, CO, CI, and SVV at each prespecified time point, will be transcribed into the CRF. The original Vital Recorder files will be archived as source documents linked to their corresponding CRFs.

To minimize missing data, participants will be observed continuously until discharge from the PACU. If a participant discontinues or deviates from the assigned intervention, outcome data will continue to be collected whenever feasible, including intraoperative hemodynamic variables, adverse events (hypotension, hypertension, bradycardia, and tachycardia), anesthetic drug doses, surgical characteristics, PACU duration, and postoperative vital signs. Reasons for non-adherence (e.g., conversion to inhalational anesthesia, conversion to open surgery, or discontinuation due to adverse events) and non-retention (withdrawal of consent or early termination) will be documented in the CRF. Participants who withdraw consent will be requested to permit use of data collected prior to withdrawal.

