### Statistical analysis

2.11

The primary outcome, TWA-MAP, will be analyzed using analysis of covariance, with group assignment as the fixed factor and baseline MAP, age, BMI, ASA-PS, and histories of hypertension and diabetes as covariates. Secondary outcomes, including hypertensive and hypotensive burden (area under the curve above or below predefined thresholds), will be compared between groups using Student’s t-test for normally distributed variables or the Mann–Whitney U test for non-normally distributed variables. Categorical outcomes, such as intraoperative hypotension, hypertension, bradycardia, tachycardia, PONV, and postoperative analgesic use, will be evaluated using the chi-square test or Fisher’s exact test, as appropriate.

Repeated-measures variables across prespecified time points (T0–T43), including HR, SBP, DBP, MAP, CO, CI, SVV, ETCO_2_, and arterial blood gas parameters, will be analyzed using generalized estimating equations (GEE) to assess group, time, and group-by-time interaction effects. An appropriate working correlation structure will be selected to account for within-subject correlations over time. As a sensitivity analysis, GEE analysis of serial blood pressure data will be performed to evaluate consistency with findings from the primary TWA-MAP analysis.

The primary efficacy analysis will follow the per-protocol (PP) principle, including all randomized participants who fully adhere to the study protocol. Participants with major protocol deviations, such as conversion to open surgery, administration of inhalational anesthetics, incomplete intraoperative hemodynamic monitoring, or early withdrawal, will be excluded from the PP analysis. Participants who discontinue the intervention due to serious adverse events will also be excluded. No intention-to-treat analysis is planned. The safety population will include all participants who receive at least one dose of the assigned anesthetic agent and will be analyzed according to the treatment actually administered.

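### The safety population requires a dose of the assigned drug but is analysed as treated, which omits anyone given only the other study drug and leaves participants given two regimens without a clear class

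*Protocol article*

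**What the plan says.** Section 2.11 (Statistical analysis) builds the safety population from participants who receive "at least one dose of the assigned anesthetic agent and will be analyzed according to the treatment actually administered". The same section removes people from the per-protocol set: "Participants who discontinue the intervention due to serious adverse events will also be excluded". It adds: "No intention-to-treat analysis is planned".

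Section 2.5 (Harms and criteria for discontinuation or modification) foresees changes of regimen during a case. Its first trigger reads: "Study interventions may be modified or discontinued in cases of severe hypotension (SBP <80 mmHg or MAP <60 mmHg) unresponsive to protocol-directed vasopressor therapy". Refractory severe bradycardia, severe hypoxemia, severe allergic reaction and the anesthesiologist's judgement that continuing is unsafe follow. In these situations "anesthesia may be transitioned to an alternative regimen", which the section does not name.

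Section 2.10 (Data management) keeps collecting outcomes and adverse events where feasible after a deviation. It gives as examples of non-adherence "conversion to inhalational anesthesia, conversion to open surgery, or discontinuation due to adverse events".

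Section 2.2 (Eligibility criteria) lists two of those same events as grounds for exclusion: "Additional exclusion criteria will include the administration of inhalational anesthetics during anesthesia and intraoperative conversion from robotic laparoscopic hysterectomy to open surgery".

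**The concern.** An as-treated rule exists mainly for the participant who received the wrong drug. Here the entry condition removes that participant before the rule can apply. The other people for whom assigned and actual treatment can differ are those exposed to more than one regimen, and for them the actual treatment has no single meaning.

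Most of the listed reasons for changing regimen are themselves safety events, so the ambiguity falls on participants whose events matter most to a comparison of hemodynamic harm. Those who stop for a serious adverse event are outside the per-protocol set, and there is no intention-to-treat set. The safety population is therefore the only defined set in which they are counted.

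The wording of section 2.2 adds a second uncertainty. Inhalational use and open conversion happen after randomization, and calling them exclusion criteria could be read as removing those participants altogether, safety included.

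**Working it through.** The plan gives no figure on this point, so the check is first logical and then illustrative.

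**Step 1. Exposure patterns against the two clauses of section 2.11, read literally**

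| Pattern | Meets the entry clause? | Class under the as-treated clause |
|---|---|---|
| A. Assigned drug only | Yes | Same as assigned |
| B. Other study drug only | No | Never reached |
| C. Both study drugs, in either order | Yes | Not determined |
| D. Assigned drug, then inhalational | Yes | Assigned arm, or no arm if classed by the later regimen |

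The clauses agree in A. In B an exposed participant is lost. In C and D the text does not settle the class. Pattern C includes both a participant switched away from the assigned drug and one started on the wrong drug and then corrected, since a single dose of the assigned agent at any time is enough for entry.

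**Step 2. Size of the ambiguity in pattern C**

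Inputs:
- 58 participants allocated 1:1 (section 2.8), taken as 58/2 = 29 per arm.
- Event counts of 3 and 0, and the number of switchers, are assumptions. The article gives neither.

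When a participant changes class, both the event and the denominator move. With k switchers who had the event, (3 − k)/(29 − k) is compared with (0 + k)/(29 + k):
- k = 0: 3/29 − 0/29 = 10.3% − 0.0% = 10.3 points.
- k = 1: 2/28 − 1/30 = 7.1% − 3.3% = 3.8 points, a shift of 6.5 points.
- k = 2: 1/27 − 2/31 = 3.7% − 6.5% = −2.7 points from unrounded values, so the sign reverses.

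Fisher's exact p-values for k = 0, 1 and 2 are 0.24, 0.61 and 1.0. None is significant, so what changes is the description of harm, not a test result.

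**Step 3. Size of the omission in pattern B**

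Assume one participant randomized to propofol receives only remimazolam and has an event, making 3 remimazolam events in all and none on propofol. A full as-treated count has 29 + 1 = 30 on remimazolam and 29 − 1 = 28 on propofol: 3/30 − 0/28 = 10.0 points. The literal rule drops that participant: 2/29 − 0/28 = 6.9 points, a shift of 3.1 points, with 57 of 58 exposed participants counted.

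**Step 4. Section 2.2 beside sections 2.10 and 2.11**

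Section 2.10 treats inhalational and open conversion as non-adherence, with follow-up continuing. Section 2.11 excludes them from the per-protocol set and does not mention removing them from safety. Only section 2.2 calls them exclusion criteria. The three sections can be reconciled, but section 2.2 as worded does not do so.

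**The case against.** The strongest reply is that pattern B hardly arises in this trial. Anesthesia providers are unblinded, the drugs look different (section 2.8), one is given by weight-based infusion and the other by target-controlled infusion (section 2.4), and adherence is reviewed weekly. An unblinded anesthesiologist would have to run the wrong drug for the whole case. This bears on frequency and stands. It does not make the sentence consistent.

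A reader might infer that the plan moves switchers to the drug given later, or to the one given for longer, and so charges a drug's worst reactions to its comparator. The article does not say this. No section classifies by later or predominant regimen, and classification by first drug would fit the words equally well. The destination of a switch is not named in section 2.5. The only conversion named, in section 2.10, is to inhalational anesthesia, which is not a trial arm, so there the event could lose its arm but could not count against the other study drug. Nor does it follow that everyone in the set started on the assigned drug.

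It can also be said that a rule for mixed exposure belongs in a statistical analysis plan, which is not shown. A detailed attribution rule could well be placed there, and its absence alone would be no criticism. The mismatch between the two clauses, however, is in the protocol's own sentence, and an analysis plan that followed it faithfully would inherit it.

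Finally, sections 2.10 and 2.11 largely show how section 2.2 is meant to work. That makes the section 2.2 wording a matter of placement, still worth correcting.

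**Conclusion.** The point holds in a limited form. What is certain is that the entry clause defeats the as-treated clause for a participant given only the other study drug. What is possible, but not prescribed, is that an event that triggered a switch ends up under another drug or under no arm.

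In the usual case, with no drug error and no switch, there is no effect. At 29 per arm, one reclassified switcher changes the difference by about 6.5 points in the example, and one omitted wrong-drug participant by about 3.1 points. Both figures rest on assumed event counts and on exact 29:29 allocation, and neither is a forecast. The importance is modest. It is raised somewhat because no other defined analysis set retains participants who stop for serious adverse events.

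**What to change.** Replace the safety-population sentence in section 2.11 with wording such as:

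> The safety population comprises every randomized participant who receives any dose of remimazolam or propofol as study drug, classified by the first study drug received. Participants who change regimen remain in that group, and each event is flagged as occurring before or after the change, using the recorded infusion times.

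In section 2.2, describe inhalational use and open conversion as post-randomization deviations that affect only the per-protocol set, in line with sections 2.10 and 2.11, so that these participants stay in the safety population. This concerns analysis sets only; the prohibition of inhalational agents in section 2.4 is untouched.

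The cost is a few sentences. No new data are needed, because section 2.9 already records infusion rates synchronized with time-stamped events. The small downside is that events after a switch count toward the first drug; the before/after flag lets a reader separate them.

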### Monitoring and interim analysis

2.12

A formal data monitoring committee (DMC) will not be established for this trial, as it is a single-center, investigator-initiated study with a relatively small sample size and short perioperative follow-up period. The safety profiles of remimazolam and propofol are well established, and both agents are routinely used in clinical practice; therefore, an independent DMC is not deemed necessary.

Interim safety oversight will be conducted by the principal investigator in collaboration with two independent senior anesthesiologists who are not involved in participant recruitment or intraoperative management. Adverse events and protocol adherence will be reviewed quarterly. Any serious adverse events will be reported immediately to the IRB and managed according to institutional policy.

No formal interim efficacy analyses are planned due to the limited sample size (n = 58) and short perioperative observation period. However, an interim review will be performed after the first 20 participants have completed the study, focusing on serious adverse events such as severe hypotension, bradycardia requiring intervention, or anaphylaxis.

No statistical stopping boundaries or alpha-spending procedures will be applied. The trial may be terminated early under the following circumstances: unexpected serious adverse events directly attributable to the study drug, safety concerns raised by the IRB, or administrative or feasibility issues such as inadequate recruitment or loss of drug supply.

Access to interim safety findings will be restricted to the monitoring team (principal investigator and independent anesthesiologists). Investigators involved in patient care, surgeons, and participants will remain blinded to group assignment during interim evaluations. The IRB will make final decisions regarding trial continuation, modification, or termination based on recommendations from the monitoring team.

### Trial monitoring

2.13

This single-center, investigator-initiated trial involves a modest sample size and short perioperative follow-up period. Therefore, a risk-based on-site monitoring approach will be implemented rather than a formal central or remote monitoring strategy. Monitoring activities will focus on verification of participant eligibility, confirmation of informed consent documentation, assessment of the completeness and accuracy of CRFs, review of key efficacy and safety endpoints, including hemodynamic parameters and adverse events, and evaluation of protocol adherence encompassing randomization procedures, blinding integrity, and anesthetic administration. Monitoring will be conducted by the principal investigator in collaboration with an independent anesthesiologist who is not involved in direct patient care. Routine monitoring will occur quarterly, with unscheduled reviews initiated if serious adverse events or protocol deviations arise. A separate monitoring plan will not be developed due to the limited scope of this single-site study. All monitoring activities will be documented, and reports will be made available to the IRB upon request.

## Discussion

3

Previous prospective randomized studies comparing remimazolam and propofol for general anesthesia have largely focused on the induction phase or on hypotension as the primary hemodynamic endpoint, rather than on continuous intraoperative blood pressure trends (Huang et al., 2023; Jeon et al., 2023; Xu et al., 2023; Kim et al., 2024; Kotani et al., 2024; Zhou et al., 2025). In addition, previous studies conducted in non-laparoscopic and non-gynecologic surgical settings reported that remimazolam was associated with a lower incidence of hypotension and more stable hemodynamic parameters compared to propofol.

In contrast, a recent retrospective study of patients undergoing laparoscopic surgery in the Trendelenburg position found that remimazolam infusion was associated with a higher incidence of intraoperative hypertension, whereas propofol infusion was more frequently associated with hypotension (Lee et al., 2025). These discrepant findings may reflect differences in intra-abdominal pressure, surgical positioning, and anesthetic management. However, because the study was retrospective and lacked standardized hemodynamic monitoring, the causal relationship between anesthetic selection and blood pressure fluctuations remains unclear.

Therefore, our randomized controlled trial is designed to address these limitations by prospectively comparing the hemodynamic effects of remimazolam- and propofol-based TIVA throughout the intraoperative period, including induction, maintenance, and emergence under standardized surgical and anesthetic conditions. By continuously monitoring intraoperative blood pressure and quantifying the TWA-MAP, as well as the cumulative burden of hypertension and hypotension, the study aims to provide a comprehensive assessment of hemodynamic stability during laparoscopic gynecologic surgery performed in the Trendelenburg position with pneumoperitoneum.

Propofol and remimazolam differ fundamentally in their cardiovascular pharmacodynamics. Propofol decreases sympathetic tone and induces vasodilation by modulating smooth muscle calcium flux, reducing total peripheral resistance and lowering arterial blood pressure (Marik, 2004; Soleimani et al., 2017; Sahinovic et al., 2018). Moreover, it diminishes left ventricular preload, leading to a reduction in stroke volume (Soleimani et al., 2017; Su et al., 2022). In addition, propofol suppresses the baroreceptor reflex, attenuating the compensatory tachycardic response to hypotension, which explains its propensity to cause hypotension and bradycardia during anesthesia (Marik, 2004; Soleimani et al., 2017; Su et al., 2022). In contrast, remimazolam induces hypnosis via γ-aminobutyric acid type A receptor modulation, with minimal impact on respiratory drive or hemodynamic stability (Hu et al., 2022; Ripoll et al., 2025). These mechanistic differences may account for the divergent intraoperative blood pressure patterns of the two agents, particularly under the physiologic alterations induced by Trendelenburg positioning and pneumoperitoneum.

Intraoperative blood pressure variability is influenced by multiple interacting factors. Patient-related variables such as age, baseline blood pressure, and comorbidities, including hypertension and diabetes, may affect overall hemodynamic stability. In addition, intraoperative factors, including blood loss, fluid shifts, surgical stimulation, head-down tilt during the Trendelenburg position, and pneumoperitoneum pressure, contribute to dynamic blood pressure fluctuations, as do the choice of anesthetic agents and the administration of vasoactive drugs (Kalmar et al., 2010; Hirsch et al., 2015; Cheng et al., 2025). Acknowledging these multifactorial influences, the study is designed to adjust for potential confounding effects by incorporating relevant covariates in the covariance analysis, to isolate the independent impact of the anesthetic agent on intraoperative hemodynamics. Intraoperative blood pressure instability, including hypotension and hypertension, has been associated with adverse postoperative outcomes. Hypotension is associated with myocardial injury, acute kidney injury, neurological complications such as postoperative stroke or delirium, and increased mortality, whereas hypertension may exacerbate intraoperative bleeding, impair surgical field visibility, and prolong operative time (Aronow, 2017; Wijnberge et al., 2021; Guarracino and Bertini, 2022; Szrama et al., 2023). Moreover, perioperative hypertension has been associated with an elevated risk of postoperative complications, including cardiovascular events, acute kidney injury, intracranial hemorrhage, and mortality (Aronow, 2017; Mohseni et al., 2022; Siripruekpong et al., 2022). Therefore, maintaining appropriate blood pressure control throughout surgery is essential to ensure adequate tissue perfusion while minimizing the risks of hypoperfusion and pressure-related injury.

The strengths of the study include its randomized, prospective design, standardized anesthetic and surgical protocols, and continuous arterial waveform–based hemodynamic monitoring using the FloTrac™ system. These features are expected to enhance the internal validity and reliability of intraoperative blood pressure assessment. Although a double-blind design is not feasible in this anesthetic trial, the single-blind approach—in which anesthesiologists are aware of group allocation but data collection and analysis are performed by blinded investigators—is intended to minimize bias and preserve the integrity of outcome assessment. Another strength of the study is the selection of a remimazolam induction regimen that reflects contemporary clinical practice and current safety considerations. Remimazolam induction will be performed at 6 mg/kg/h, which is within the approved dosing range and lower than the maximum recommended induction rate of 12 mg/kg/h. This dosing strategy was chosen in consideration of emerging evidence suggesting that lower induction infusion rates may reduce the risk of adverse events while maintaining satisfactory anesthetic conditions (Lee and Kim, 2024).

The study has several limitations. First, it will be conducted at a single secondary care hospital and will include only relatively healthy female patients undergoing elective gynecologic laparoscopic surgery. Therefore, the generalizability of the findings may be limited, particularly to populations with different demographic or clinical characteristics. Second, the relatively modest sample size, although determined based on an *a priori* power calculation for the primary outcome, may limit statistical power for secondary outcomes and exploratory analyses. Therefore, the findings should be interpreted with appropriate caution. Third, transient blood pressure artifacts related to surgical manipulation or device calibration cannot be entirely avoided; however, predefined data-cleaning criteria will be applied to mitigate their impact. Fourth, postoperative long-term outcomes will not be evaluated in this study. Finally, a limitation of this study is the difference in drug delivery methods between study groups. Remimazolam will be administered by continuous infusion because no externally validated PK/PD-linked target-controlled infusion model is currently available for routine clinical use, whereas propofol will be administered using a target-controlled infusion system. Although this approach reflects contemporary anesthetic practice and enhances the clinical applicability of the study design, differences in administration strategy could influence anesthetic exposure and hemodynamic responses. Future studies employing validated PK/PD-guided administration methods for remimazolam may allow more direct comparisons between anesthetic agents.

Despite these limitations, the study is expected to provide high-quality evidence regarding the differential hemodynamic effects of remimazolam and propofol during laparoscopic gynecologic surgery. The findings may help anesthesiologists optimize anesthetic drug selection and intraoperative blood pressure management strategies, enhancing hemodynamic stability and improving patient safety in minimally invasive surgery.

